## Protocol Synopsis

### Study Objective

This study aims to examine the efficacy of a brain-computer interface (BCI) system for the treatment of inattentive symptoms of Attention Deficit Hyperactivity Disorder (ADHD). Our hypothesis is that children with ADHD receiving treatment with the BCI-based training will improve to a greater extent than the control group.

### Study Population

This study will enroll ADHD children aged 6 to 12 referred from Child Guidance Clinic (CGC)

#### Eligibility Criteria

The child should satisfy the following inclusion criteria:

1. Between the age of 6 and 12 years old inclusive.
2. Satisfy the following criteria for the diagnosis of ADHD:
  - Meets criteria for ADHD, combined or inattentive subtypes based on the Computerized Diagnostic Interview Schedule for Children (C-DISC).

They should not have any of the following exclusion criteria:

1. Present or history of medical treatment with stimulant medication and Atomoxetine in the past 1 month.
2. Present or regular intake of polyunsaturated fatty acids supplement intake (e.g. Omega-3 oil, flax seed oil, cod liver oil) for more than 2 weeks in the past 3 months.
3. Present or history of traditional Chinese medicine (TCM) prescribed for treatment of attention problems in the past 1 month.
4. Co-morbid severe psychiatric condition or known sensory-neural deficit e.g. complete blindness or deafness.
5. History of epileptic seizures.
6. Known to have developmental delay (i.e. IQ 70 and below).
7. Predominantly hyperactive/impulsive subtype of ADHD.

### Research Related Activities

Subjects will complete structured interviews, questionnaires and undergo assessments in the clinic.

Intervention for the subjects will include the following:

1. BCI training protocol.

Assessments for the participants involved will include the following:

1. Children: KBIT-2, Conner's Continuous Performance Test, 2nd Edition (CPT-II).
2. Parents: C-DISC, Attention Deficit Hyperactive Disorder- Rating Scale (ADHD-RS) and Child Behaviour Checklist (CBCL).

3. Clinicians: ADHD-RS, Clinical Global Assessment Scale (C-GAS), Clinical Global Impression Severity Scale (CGI-S), Clinical Global Impression Improvement Scale (CGI-I) and Pediatric Adverse Event Rating Scale (PAERS).

## **1. Background and Rationale**

ADHD is the most common psychiatric condition among children and adolescents seen at the CGC in Singapore much like the rest of the world. ADHD is diagnosed clinically and is characterised by symptoms of inattention and/or hyperactivity/ impulsivity, with onset in childhood (1). Community studies have found the prevalence of ADHD to be between 1.7% and 16% (2). Recent studies demonstrated that up to half of the children with ADHD continue to have symptoms in adulthood (1, 3). Male-female ratios range from 9:1 to 6:1 in clinical samples but are about 3:1 in community-based population studies (4). ADHD is associated with academic underachievement, work difficulty, social rejection, driving accidents, smoking, alcohol and drug abuse, and poor self esteem. In view of the prevalence, persistence and long term impairment, ADHD is an important public health problem. About 500 new cases of ADHD are referred to CGC annually for treatment, and the number is still increasing.

Management of ADHD includes pharmacological and behavioural management. Pharmacological treatment includes stimulant and non-stimulant medications (1, 5). Methylphenidate is the only stimulant medication available in Singapore. Parents are often concerned about its side effects including poor appetite, physical growth retardation and cardiovascular effects. Being a potential drug of abuse, methylphenidate is also avoided in patients who may be likely to abuse the medication. On the other hand, Atomoxetine, a relatively new non-stimulant medication, is expensive with significant side effects. Atomoxetine carries a 'black box label' warning of potential increased suicidal thinking associated with its use. Behavioural management, though important, has been shown to be less superior to pharmacological treatment (6). Follow-up results of the NIMH Collaborative Multisite Multimodal Treatment Study of Children With Attention-Deficit/Hyperactivity Disorder (MTA) showed that despite initial symptom improvement during treatment, the superiority of medication was lost by 3 years, and the 8-year follow up showed that children with combined-type ADHD exhibit significant impairment in adolescence (7).

BCI is a direct communication pathway between a human brain and an external device. It is a technology that enables people to interact with computers through their thoughts.

Electroencephalogram (EEG) is the best studied non-invasive interface facilitating such communication, mainly due to its fine temporal resolution, ease of use, portability and low set-up cost. It presents the user with real-time feedback on brainwave activity, as measured by electrodes on the scalp, typically in the form of a video display, sound or vibration (8). In children with ADHD, reduced levels of the higher-frequency brain waves are especially noticeable in the prefrontal cortex, an area involved in attention control. They also have an increase in lower-frequency waves, especially theta waves from 4 to 7.5 Hz. Neuro-feedback, a form of biofeedback programme (9, 10, 11), has been used in a limited fashion but is not well studied.

### **1.1 Rationale and justification for the Study**

We have developed a series of BCI-based training activities incorporating our patented attention detection technology into interactive games for the treatment of ADHD. As the BCI extracts a quantifiable attention level from EEG, users can employ their attention to play these games directly.

Therefore, there is no need for the users to follow any prompt or output on the screen; in other words, this works in an 'asynchronous' mode. With such a mode, user can start to play the game straightaway, without any learning. At the same time, since the user can control a game without any feedback (auditory or visual) there is a unique feed-forward mechanism as well. To help the user progress through the series of activities of increasing difficulty, players will first need to master a simple concentration task before moving on to the next task according to the treatment protocol. Most therapy involves at least a total of 20 sessions (11); as such, our intervention protocol includes 20 sessions followed by 3 one-monthly 'booster training'. The treatment protocol also involves a homework task for every alternate session, during which the child will be 'trained' to use their newly-acquired concentration skill during everyday tasks. Our intervention and treatment protocol requires little training for the therapist, and the equipment required is simple and portable.

A pilot non-randomized trial to test the treatment protocol and its efficacy was conducted on 10 children with ADHD. Another 10 children with ADHD were recruited as controls. The 20-session intervention program was well accepted by the parents and children. The ADHD scales administered by parents and teachers both showed good test-retest reliability (>0.9). We have found satisfactory level of compliance to the intervention protocols.

Therapy using non-invasive BCI system-based games may represent one alternative means to treat children with ADHD symptoms. If demonstrated to be efficacious, parents are likely to prefer this as an alternative to current treatment modalities of medications (with potentially serious side effects) and behavior management (parents generally find this difficult and challenging). Children themselves are also more likely to enjoy the treatment and hence, comply better.

In the longer term, this approach and system may have potential for attention and cognitive enhancement for patients with cognitive impairment or early dementia.

## **2. Hypothesis and Objectives**

### **2.1.1 Primary Objective**

This study aims to examine the efficacy of a brain-computer interface system for the treatment of inattentive symptoms of Attention Deficit Hyperactivity Disorder (ADHD). The hypothesis is that children with ADHD receiving treatment with the BCI-based training will improve to a greater extent than the control group.

### **2.1.2 Primary Endpoint**

The primary outcome of this study will be the change in the inattentive score on the ADHD Rating Scale as rated by the clinicians from week 1 to week 8.

### **2.2.1 Secondary Objectives**

- To investigate the sustainability of the effect of a brain computer interface system for the treatment of inattentive symptoms of Attention Deficit Hyperactivity Disorder (ADHD).

- To investigate the effect of a brain computer interface on daily functioning.
- To investigate if there is any safety concern related to the use of BCI.

### 2.2.2 Secondary Endpoints

- 1) The change in the inattentive score of the ADHD RS rated by parent from week 1 to week 8.
- 2) The change in the inattentive score of the ADHD RS rated by clinician and parent from week 1 to week 8, week 1 to week 20 and week 1 to week 24 for the intervention group and week 8 to week 16, week 8 to week 28 and week 8 to week 32 for the control group.
- 3) The change in parent rated CBCL inattention score from week 1 to week 8.
- 4) The change in parent rated CBCL inattention score from week 1 to week 8, week 1 to week 20 and week 1 to week 24 for the intervention group and week 8 to week 16, week 8 to week 28 and week 8 to week 32 for the control group.
- 5) The change in clinician rated CGAS and CGI scores from week 1 to week 8.
- 6) The change in clinician rated CGAS and CGI scores from week 1 to week 8, week 1 to week 20 and week 1 to week 28 (intervention group) and week 8 to week 16, week 8 to week 28 and week 8 to week 32 (control group).

### 2.3.1 Safety Endpoints

Adverse events and serious adverse events.

### 2.4.1 Exploratory analysis

Investigate the level of agreement in symptom severity among reports from parents and clinicians, as well as performance on CPT.

## 3. Study Population

This study will enroll 172 children age 6 to 12 years with ADHD.

### 3.1 Inclusion Criteria

A subject will be eligible for inclusion in the study if ALL of the following criteria apply:

1. The child should be between the age of 6 and 12 years old inclusive
2. The child should satisfy the following criteria for the diagnosis of ADHD:
  - Meets criteria for ADHD, combined or inattentive subtypes based on the Computerized

Diagnostic Interview Schedule for children (C-DISC)

### 3.2 Exclusion Criteria

A subject will not be eligible for inclusion in the study if ANY of the following criteria apply:

1. Present or history of medical treatment with stimulant medication and Atomoxetine in the past one month.
2. Present or regular intake of polyunsaturated fatty acids supplement intake (e.g. Omega-3 oil, flax seed oil, cod liver oil) for more than 2 weeks in the past 3 months.
3. Present or history of traditional Chinese medicine (TCM) prescribed for treatment of attention problems in the past 1 month.
4. Co-morbid severe psychiatric condition or known sensory-neural deficit e.g. complete blindness or deafness (such that they cannot play computer games).
5. History of epileptic seizures.
6. Known to have developmental delay (i.e. IQ 70 and below).
7. Predominantly hyperactive/impulsive subtype of ADHD (i.e. no predominant inattentive symptoms).

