## **8. Treatment of Subjects**

### **8.1 Specific Restrictions**

1. There are no dietary restrictions.
2. There is no limitation in the physical activity of the subject.
3. Intake of methylphenidate, atomoxetine and tricyclic anti-depressant are to be avoided 1 month before and during the study since these medications can improve ADHD symptoms. The parent/legal guardian and/or the subject will be asked about this during each study visit. If there is a need for these medications to be prescribed to the subject then the subject will be withdrawn from the study.
4. Intake of polyunsaturated fatty acids (PUFA) supplement intake (e.g. Omega-3 oil, flax seed oil, cod liver oil) which can improve ADHD symptoms are also to be avoided 3 months before and during the study. These supplements are receiving attention as a complementary approach to managing ADHD. While not a primary empirical based treatment and efficacy outcome varied, the study team will exclude subjects who are taking these supplements in the past 3 months, if they have been taking them regularly for a period longer than 2 weeks, to ensure that any improvement in inattentive symptoms is not due to the supplementation.
5. Intake of traditional Chinese medication (TCM) treatment is also to be avoided 1 month before and during study. Similar to PUFA, these alternative treatments could also manage inattentive symptoms. Therefore, subjects will be withdrawn from the study if these supplements are taken in the past 1 month.
6. From the literature, the potential risks to the BCI may include seizure or destabilization of the individual's mood state. To minimize such risk, subjects with history of seizure or severe psychiatric disorder will be excluded in this study.

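### Section 3.2 and the synopsis exclude less at entry than section 8.1 restricts before the study (tricyclics; TCM not given for attention), so a child can be randomised while already in breach

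*Protocol*

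**What the plan says.** **Entry criteria.** Section 3.2 item 1 excludes "Present or history of medical treatment with stimulant medication and Atomoxetine in the past one month". The synopsis has the same criterion: "Present or history of medical treatment with stimulant medication and Atomoxetine in the past 1 month". Neither list names tricyclics. For TCM, section 3.2 item 3 reads "Present or history of traditional Chinese medicine (TCM) prescribed for treatment of attention problems in the past 1 month".

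**Pre-study and on-study restrictions.** Section 8.1 item 3 reads "Intake of methylphenidate, atomoxetine and tricyclic anti-depressant are to be avoided 1 month before and during the study", and gives as its reason that these drugs can improve ADHD symptoms. It continues: "If there is a need for these medications to be prescribed to the subject then the subject will be withdrawn from the study". On TCM, item 5 reads "Intake of traditional Chinese medication (TCM) treatment is also to be avoided 1 month before and during study", and later adds that "subjects will be withdrawn from the study if these supplements are taken in the past 1 month".

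**Other relevant text.** Section 3.3 item 3 names tricyclics, PUFA supplements and TCM as possible grounds for withdrawal from the intervention during the trial period, at the Principal Investigator's discretion. Section 6.4 randomises once consent and assent are signed and eligibility is confirmed. Section 8.2 records restricted drugs taken in the month before screening. Section 11.2.1 defines the ITT set as all randomised subjects.

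**The concern.** A washout does its job only if it is applied before allocation. Here the list that controls randomisation is shorter than the list of products that the protocol wants absent before the study. Staff who follow 3.2 correctly can therefore randomise a child whom 8.1 already treats as non-compliant, on information available at screening.

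Once randomised, the child belongs to the ITT set. If the child then leaves, the trial loses an outcome for a reason that could have been settled beforehand. If the child stays, a product that the protocol itself regards as able to improve ADHD symptoms may affect the primary endpoint, the week 1 to week 8 change in the clinician-rated inattentive score. Two staff members working from different sections could also treat similar children differently.

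**Working it through.** The point rests on comparing passages, not on a calculation.

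**1. The gate.** Section 6.4 requires signed consent and assent and confirmed eligibility criteria. Those criteria are in 3.1 and 3.2, with a copy in the synopsis. None of them refers to 8.1.

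**2. The lists side by side.**

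| Product | Entry (3.2 and synopsis) | Before the study (8.1) | Result |
|---|---|---|---|
| Tricyclics | not listed | avoid for 1 month (item 3) | clear mismatch |
| TCM | 1 month, only if prescribed for attention problems | avoid for 1 month, no indication stated; withdrawal wording looks back 1 month (item 5) | mismatch as literally worded |
| PUFA | present intake, or regular intake for more than 2 weeks in 3 months | avoid for 3 months, then the same threshold of more than 2 weeks (item 4) | ambiguity at most |

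**3. Two test cases.** A child taking a tricyclic at screening meets no drug exclusion in 3.2, can be randomised under 6.4, and is in breach of 8.1 item 3. A child given TCM for a complaint other than attention in the past month is eligible under 3.2 item 3, and comes within both the avoidance and the withdrawal sentences of 8.1 item 5.

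**4. Does other text close the gap?** Exclusion 4 (severe psychiatric comorbidity) concerns a diagnosis, not a drug. Section 3.3 item 3 names tricyclics but applies only during the trial. Section 8.2 records use in the CRF and does not make it an exclusion. Its cross-reference to section 9.1 item 3 leads to the safety definitions, not to 8.1, which suggests that these sections were not aligned.

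**5. Size.** The documents give no rate of tricyclic or TCM use. For context, the planned sample size reproduces. With effect size 0.5, two-sided 5% and 80% power, n = 2 × (1.96 + 0.84)² / 0.5² gives 63 per group, or 64 with the t distribution. Dividing by 0.8 gives 79 or 80, against the stated figure of about 80. Enrolment is 86 per arm, so 86 − 64 = 22 per arm could be lost before the number falls below 64. A 20% loss would be 0.20 × 86 = 17.2 per arm.

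Purely as an assumption, suppose that 3% to 10% of children had used a tricyclic or any TCM in the month before entry. That is 0.03 × 86 = 2.6 to 0.10 × 86 = 8.6 per arm (about 5 to 17 of 172 in total). Even if all were lost, they would use between 2.6/17.2 = 15% and 8.6/17.2 = 50% of the 20% allowance. The range has no basis in the protocol and depends on the literal reading of the TCM wording.

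**The case against.** The best defence is that 8.1 was meant to operate at entry. Items 4 and 6 speak of excluding subjects, and 8.2 records restricted drugs with the stated aim of making sure that subjects are not on them. For TCM, item 5 gives its reason in terms of inattentive symptoms, and 3.3 item 3 is limited to products that can improve ADHD symptoms. Read together, these could confine the TCM restriction to attention-related use, as in 3.2. This weakens the TCM example. It does not remove it, because the avoidance and withdrawal sentences themselves carry no indication limit. It does not repair the tricyclic omission: intent in 8.1 is not an exclusion criterion.

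Some stronger readings are tempting, but the documents do not support them:

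- **That every such child would have to be withdrawn.** The withdrawal sentence in 8.1 item 3 concerns a need to prescribe, and 3.3 item 3 is discretionary and limited to the trial period. A tricyclic stopped before entry breaches the avoidance rule but triggers neither. Section 3.3 also keeps collecting data after withdrawal from the intervention, unless the family leaves the study altogether.
- **That the PUFA rules contradict each other.** Section 8.1 item 4 repeats the 3.2 threshold when it says who is excluded, and the entry wording can be read as barring current use.
- **That criterion 1 requires use of both drugs.** The conjunction is a drafting matter. Section 8.1 item 3 uses the same list form, and its intent is plain.
- **That the primary comparison is biased.** Use before entry precedes a 1:1 random allocation and is balanced in expectation. The expected cost is noise and loss.

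**Conclusion.** The mismatch is real. It is clear for tricyclics, which are restricted before the study in 8.1 and named in 3.3 but absent from both entry lists. It holds for TCM on the literal wording. For PUFA there is no more than an ambiguity within 8.1 item 4.

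The consequence is that children in breach at screening can enter an all-randomised ITT set, where they add avoidable loss or variability to the week 1 to week 8 change. How many is unknown, and the conclusion does not depend on a count. It assumes only that site staff apply 3.2 as written when they confirm eligibility. This is an inconsistency worth correcting. It is not evidence that the primary analysis is invalid or the trial underpowered.

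**What to change.** Reconcile section 3.2, the synopsis, section 3.3 item 3 and section 8.1 items 3 to 5 so that they share one list of products and look-back windows. Use that list both as the exclusion criterion and as the pre-study restriction, and confirm it on the eligibility checklist before the randomisation call. State whether the TCM restriction depends on indication, make the two PUFA sentences in 8.1 item 4 agree, and correct the cross-reference in 8.2. Which products, windows and withdrawal rule apply is for the sponsor and investigator to decide.

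The cost is protocol wording and one checklist line. Depending on which text is kept, there will be either a few more screen failures or a slightly less strict washout.

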### 3.3 Withdrawal Criteria

Subjects may be withdrawn from the intervention according to the discretion of the Principal Investigator if:

1. ADHD-RS raw score increases by 25% as rated by clinicians, and/or
2. CGI-S scores are between 5 and 7 inclusive.
3. Receive any medication (e.g. methylphenidate, atomoxetine, tricyclic anti-depressant, and/or polyunsaturated fatty acids (PUFA) supplement (e.g. Omega-3 oil, flax seed oil, cod liver oil), and/or traditional Chinese medication (TCM) which can improve ADHD symptoms during the trial period. The parent/child will be asked about this each time they turn up at the clinic.

All recruited subjects are free to withdraw consent and discontinue participation without penalty and without providing reasons. However data collection will continue after withdrawal from intervention unless the subject or parents/legal guardians decide to withdraw from the study totally (this will be explicitly asked again upon withdrawal).

Participants can still choose to continue or discontinue with the remaining assessments at Week 1, 8, 16 (control), 20 (intervention), 24 (intervention), 28 (control), and 32 (control) despite having BCI training sessions being ceased.

Subjects will be considered as 'drop-outs' if they:

1. Become lost to follow-up or discontinues intervention.

## 4. Trial Schedule

During Pre-Screening, the parent/legal guardian will complete the structured interview, CDISC.

Once the diagnosis of ADHD (inattentive/combined subtype) has been made, the parent/legal guardian will complete the following questionnaires during the baseline stage (Week 1):

a. ADHD Rating Scale

b. Child Behavior Checklist

If the child has ever been placed in the school's Learning Support Program and/or is currently failing a subject, he/she will be screened using the Kaufman Brief Intelligence Test.

The assessment schedule is summarized in Table 1 section 6.6.

Once the diagnosis of ADHD has been made, the following assessments will be completed by different informants:

CLINICIAN:

1. ADHD Rating Scale (ADHD- RS)
2. Clinical Global Assessment Scale (CGAS)
3. Clinical Global Impression - Severity Scale (CGI-S)
4. Clinical Global Impression – Improvement Scale (CGI-I)
5. Pediatric Adverse Event Rating Scale (PAERS) from week 8 onwards as there will be nothing to report at the first session.

PARENT:

1. ADHD Rating Scale (ADHD-RS)
2. Child Behavior Checklist (CBCL)

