### **5.2 Control Group**

86 subjects in the control group will not receive BCI training during the first 8 weeks of their study participation; they will act as controls. At week 9, subjects in this group will go through the BCI training similar to the intervention group. If sessions are missed during the 8-weeks period due to unforeseen circumstances (e.g. sickness, travel plans), arrangements will be made for participants to attend up to 5 BCI-based therapy sessions per week. All participants will have to complete a minimum of 20 sessions within the 8-weeks period for treatment efficacy.

They will take part in a total of 24 sessions spread over an 8-week period, followed by one-monthly booster sessions for another 3 months. Subjects will be tasked to do a set of MCQs on the computer. The task will consist of both Math and English questions and will be matched to their grade level. The procedure for MCQ administration will be exactly the same as the intervention group. Administering of MCQs will be done at the end of alternate intervention sessions over the 8-week period and during each

of the 3 monthly 'booster' sessions. Their EEG activity will be recorded during these tasks as well. Their participation in the research study will last 8 months. The subjects in the control group will complete the exact same questionnaires at the same time-points as the intervention group.

All children in this group will be followed up by their child psychiatrist at the following weeks: Week 1, 8, 16, 28 and 32.

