| Clinical Global Impression - Improvement Scale                            | Group 1     |                     | XX       | XX           |              | X       |             | X         |         |
|                                                                           | Group 2     |                     |          |              | X            |         | X           |           | X       |
| ADHD Rating Scale                                                         | Group 1     |                     | XX       | XX           |              | X       |             | X         |         |
|                                                                           | Group 2     |                     |          |              | X            |         | X           |           | X       |
| Pediatric Adverse Event Rating Scale (PAERS)                              | Group 1     |                     |          | X            |              | X       |             | X         |         |
|                                                                           | Group 2     |                     |          |              | X            |         | X           |           | X       |

NB: All assessment visits will be completed accordingly to the assessment week within the window period of +/- 5 working days.

Figure 1: Study Visit and Procedure for Both Groups

**Appendix A****Schedule 1: Gantt schedule of Phase 2 overall study design and timelines for intervention & control groups.**[figure not shown]**Assessments for both intervention and control group**

| Week 0                      | Week 1
(+/- 5 work days)   | Week 8
(+/- 5 work days)                              | Week 16
(+/- 5 work days)  | Week 20 (Intervention)
Week 28 (Control)
(+/- 5 work days) | Week 24 (Intervention)
Week 32 (Control)
(+/- 5 work days) |
|------------------------------------|---------------------------------------------|------------------------------------------------------------------------|---------------------------------------------|-----------------------------------------------------------------------------------------------------|-----------------------------------------------------------------------------------------------------|

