## **9. Safety Measurements**

### **9.1 Definitions**

#### **9.1.1 Adverse Events**

The Pediatric Adverse Event Rating Scale will be used to assess adverse events.

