## **9.2 Collection, Recording and Reporting**

### **9.2.1 AE**

AEs will be collected from the time the informed consent and assent forms have been signed until the end of the study. This will include AEs spontaneously reported by the subject and / or observed by the parents and clinicians.

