#### **11.2.3 Analysis of primary and secondary endpoints**

Change in the inattentive score on the ADHD Rating Scale as rated by clinicians at week 8 will be compared between the intervention group (post-BCI) and control groups (pre-BCI) using the two sample t test. Mean difference of the changes between the two groups and its associated 95% confidence interval will be reported. Comparison of change scores for the continuous secondary outcomes at week 8 between the two groups will also be conducted by using the two sample t test or Mann-Whitney U test, where appropriate. Chi squared test or Fisher's exact test, where appropriate, will be used for categorical secondary outcomes.

Booster effect will be analyzed by first pooling paired data before and after the boosters in the two groups. Change in efficacy endpoints as rated by clinicians and parents at week 20 from week 1 in the intervention arm and changes at week 28 from week 9 in the waitlist control group. These pooled changes before and after the boosters will be summarized; and comparisons of efficacy endpoints pre and post boosters will be made in the pooled data by using the paired t test or Wilcoxon signed rank test, where appropriate. The above will also be conducted at week 24 from week 1 in the intervention arm and week 32 from week 9 in the waitlist control to assess the effect the sustainability of the effect of the BCI system.

The longitudinal ADHD ratings, and other clinician's scales will be explored by the generalized estimating equations approach, both assessing the time trend and the difference in time trend between groups.

Frequency and percentage of the adverse events highlighted in the side effect checklist will be summarized for the pooled sample since the BCI program is administered to all subjects for all those that receive at least one BCI session.

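### With no week 1 PAERS rating and adverse events reported as one pooled percentage, the plan cannot show whether BCI raised common complaints

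*Protocol*

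**What the plan says.** - **Objective.** Section 2.2.1 lists as a secondary objective: "To investigate if there is any safety concern related to the use of BCI". The safety endpoints in 2.3.1 are adverse events (AEs) and serious adverse events (SAEs).
- **Instrument.** Section 9.1.1: "The Pediatric Adverse Event Rating Scale will be used to assess adverse events".
- **Start of rating.** Section 4 has clinicians complete the PAERS "from week 8 onwards as there will be nothing to report at the first session". Table 1 in 6.6 has no baseline mark for it in either arm. As printed, the intervention arm is rated at weeks 8, 20 and 24 and the control arm at weeks 16, 28 and 32.
- **Control arm at week 8.** Section 4 makes no distinction between arms. Section 5.2 adds: "The subjects in the control group will complete the exact same questionnaires at the same time-points as the intervention group". Table 1 shows no control PAERS at week 8.
- **Other collection.** Section 9.2.1: "AEs will be collected from the time the informed consent and assent forms have been signed until the end of the study". This covers spontaneous reports and observations by parents and clinicians.
- **Analysis.** Under 11.2.3, frequencies and percentages of events from the side effect checklist "will be summarized for the pooled sample since the BCI program is administered to all subjects". The table is limited to children who had at least one session.
- **Named risk.** Section 8.1, item 6: "the potential risks to the BCI may include seizure or destabilization of the individual's mood state".

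**The concern.** The protocol fixes two choices and gives a reason for each. Neither reason holds.

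The first is that a week 1 rating would find nothing. That is true of BCI effects but not of complaints. Section 3.2 excludes only severe psychiatric comorbidity, so milder mood symptoms can be present at entry, and mood is one of the two risks that 8.1 names. A complaint that a child brings into the trial cannot later be told from one that began under BCI.

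The second is that pooling is justified because everyone receives BCI. That is true over the whole trial but not in weeks 1 to 8, when the control arm is untreated (sections 5 and 5.2). Those weeks hold the only randomised comparison of BCI with no BCI.

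The objective asks about events related to BCI, which is a question of attribution. With neither a baseline nor a comparator, the reader may take ordinary background complaints for device effects, or dismiss a real increase as background.

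**Working it through.** **The plan's own figure.** The documents give no number for the safety analysis. The one calculation, about 80 per group in 11.1, concerns the primary efficacy endpoint. It reproduces: 2 × (1.96 + 0.84)² / 0.5² gives 63 per arm, and 63/0.80 = 79; the t-based version gives 64, and 64/0.80 = 80. It has no bearing on this point.

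**Inputs.** 172 children, 86 per arm (sections 3, 5.1, 5.2 and 6.4); up to 20% losses (11.1), so 172 × 0.8 ≈ 138 in total and 86 × 0.8 = 68.8, taken as 68 per arm. The background rate b, meaning the share of children who would be listed for a given complaint without BCI, is not in the documents. I assume 5 to 40%. I also take the side effect checklist in 11.2.3 to be the PAERS.

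**Step 1: what the pooled figure estimates.** If BCI adds a share a, the pooled percentage is b + a. One number cannot give both. A pooled 20% fits equally well with
- b = 20%, a = 0;
- b = 10%, a = 10 points;
- b = 5%, a = 15 points.

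**Step 2: children listed when BCI does nothing.** The expected count is 172 × b. At b = 20% this is 34.4, and the 95% interval for the percentage is 20 ± 1.96 × √(0.20 × 0.80/172) = 20 ± 6.0, or 14 to 26%. A narrow interval does not help, because it surrounds b + a. With 138 children the counts are about 7, 14, 28 and 55 for b = 5, 10, 20 and 40%.

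**Step 3: what the randomised comparison could estimate.** The 95% half-width for the difference between arms, with both near b, is 1.96 × √(2b(1 − b)/n). At b = 20% and n = 86: 1.96 × √(0.32/86) = 1.96 × 0.0610 = 12.0 points.

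**Step 4: what it could detect.** Power is Φ[(d − 1.96 × SE0)/SE1], with d the difference, SE0 the standard error under no difference (pooled rate) and SE1 that under the alternative. For 20% against 39.4% with 86 per arm: SE0 = 0.0697, SE1 = 0.0681, and (0.194 − 0.137)/0.0681 = 0.84, so power is 80%.

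| Assumed b | Listed of 172, no BCI effect | Half-width, 86 per arm | Half-width, 68 per arm | BCI-arm rate detectable with 80% power, 86 per arm |
|---|---|---|---|---|
| 5% | 9 | 6.5 points | 7.3 points | 19% |
| 10% | 17 | 9.0 points | 10.1 points | 26% |
| 20% | 34 | 12.0 points | 13.4 points | 39% |
| 40% | 69 | 14.6 points | 16.5 points | 61% |

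**Step 5: does the week 8 comparison exist?** On section 4, and on 5.2 if it extends to clinician-rated forms, controls are rated at week 8. That rating would also be their last before BCI starts in week 9. On Table 1 as printed they are first rated at week 16, after their BCI course, so no child in either arm has a rating before BCI and there is no untreated checklist data at all. These places must be reconciled before step 3 can apply to PAERS items.

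**The case against.** Four arguments can be made for the plan.

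**The plan is not silent on safety.** SAEs, spontaneously reported AEs (9.2.1), the causality criteria for unanticipated problems (9.1.2) and follow-up of events (9.3) all bear on the objective. The CBCL, CGAS and CGI-S are rated at weeks 1 and 8. This stands. A reader might infer that the safety objective cannot be answered at all; the documents do not support that. The loss is confined to attributing common checklist complaints.

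**Wait-period complaints may never reach the table.** A reader might infer that events in untreated controls are counted as BCI events. That is not established. Section 11.2.3 tabulates checklist events and does not say that spontaneous reports feed in, and Table 1 gives controls no PAERS before week 16. Nor does the table label its events as caused by BCI. Even so, 11.2.3 selects children by exposure, not events by onset, so if such events did enter the table no stated rule would remove them. If they do not, the comparator is missing.

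**Starting the checklist late does not contradict 9.2.1.** A reader might see a conflict with collecting AEs from consent. There is none: one sentence schedules a form, the other opens spontaneous reporting. The reason given for the late start is weak, but that is a different fault.

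**Details belong in the SAP, and the form is not shown.** Definitions of treatment-emergent events are commonly left to the SAP, and the PAERS form may ask about onset or relatedness. Both are fair. But the protocol itself fixes the pooled summary and its reason, and no SAP can recover a baseline that was not collected.

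**Conclusion.** The point holds in limited form. Table 1 gives neither arm a PAERS rating before BCI, and section 4 rules out week 1 in any case. The stated pooled percentage cannot separate background complaints from BCI effects, and the randomised untreated weeks go unused. At assumed background rates of 5 to 40%, about 9 to 69 of 172 children would be listed with no BCI effect. A week 8 comparison would put the excess within about ±6.5 to 15 points at 86 per arm.

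These figures rest on assumed background rates, on every child being treated and rated, and on the form scoring complaints that are already present. The comparison is only moderately precise: it would detect large excesses, not small ones.

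A reader might also infer that subtracting a baseline would bring the figure to zero when BCI is harmless. It would not, because new background complaints arise over 24 or 32 weeks. That is why the comparison by arm is needed as well as the baseline. The primary efficacy result is unaffected.

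**What to change.** 1. In section 4 and Table 1, add the PAERS at week 1 in both arms and delete the stated reason for omitting it.
2. Reconcile section 4, section 5.2 and Table 1 so that both arms are rated at week 8. Without this, step 1 gives a baseline but no checklist comparison.
3. In 11.2.3, replace the pooled-only summary with (a) PAERS items and AEs from weeks 1 to 8 by randomised arm, with the difference and its 95% interval, and (b) a pooled table limited to events that are new, or worse than the child's last rating before BCI, after the first BCI session. State whether spontaneously reported AEs enter these tables.

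The cost is one short form at week 1, and one at week 8 for controls if Table 1 is the current intent. Both fall at visits where the clinician already completes other scales. Beyond that it needs a Table 1 amendment and a few extra tables. It has to be done before enrolment, since a missing baseline cannot be filled in later.
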